##### Qualitative analysis

Transcribed interviews will be analysed using an inductive thematic analytic approach [46]. Rather than relying on a pre-existing coding or theoretical framework, codes and themes will be data-driven. A number of strategies will be employed to enhance the credibility and methodological rigour of the analysis, including the use of reflexive practices in supervisory discussion and presentation of the analysis to a small group of expert researchers and therapists.

#### Health economics analysis

In order for a new intervention to be widely adopted in the NHS, it is necessary to assess not only its clinical effectiveness but also its cost-effectiveness, namely whether the new intervention is good value for money compared with current practice. In other words, the performance of an economic evaluation alongside this RCT will allow us to establish whether OSI+therapist support is worth doing compared with C-TAU and whether we are satisfied that the health care resources required for OSI+therapist support to be made available to those who could benefit from it should be spent this way rather than some other way, i.e. C-TAU in this specific case. Therefore, the results of the economic evaluation will be invaluable to inform NHS decisions for treating child anxiety in such challenging circumstances and beyond.

The economic aspects of the study are summarised in this protocol. Details will be fully described in a health economics analysis plan (HEAP) [47], which will be finalised before any analysis takes place.

The economic evaluation will comprise cost-utility analysis (CUA) as primary analysis and cost-effectiveness analysis (CEA) as secondary analysis. They will be conducted from the NHS and personal services perspective (base-case analysis) as per NICE recommendations [38]. A wider societal perspective (including parental health care resource use and work productivity and school impacts) will be adopted in sensitivity analyses. We will follow best-practice guidelines for conducting and reporting economic evaluation analyses [38, 48]. Both an intention-to-treat and per-protocol approach will be adopted for primary and secondary analyses, as it is common in inferiority trials [49–51]. Missing data will be imputed by use of conditional mean imputation for missing values deemed highly deterministic (e.g. online/ face-to-face therapist contacts), and multiple imputation for other variables (e.g. GP consultations) under the assumption of missing at random. In the cost-utility analysis, the health outcomes will be quality-adjusted life years (QALYs) gained for the child (base-case analysis), and for the parent-child dyad (sensitivity analysis). QALYs will be derived from the collected measures CHU-9D [39] for the child, and EQ-5D-5L [35–38] for the parent.

In the secondary cost-effectiveness analyses, two outcomes will be considered, namely the primary clinical outcome (CAIS-P), and the percentage of school attendance. For each participant, components of treatment costs and other individual, family, and wider societal costs (as collected using the economic logs completed by therapists/ parents) will be computed by multiplying units of resource use by their unit costs and then summed to obtain a total cost per patient. Unit costs for health, social care, and other resources will be mainly derived from local and national sources [52] and estimated in line with best-practice. Costs will be expressed in pounds sterling at current prices. Given the short time-frame of the trial and follow-up, discounting will not be applied to costs or effects. The incremental costs and effects will be reported using incremental cost-effectiveness ratios (ICERs), where appropriate, and presenting cost-effectiveness acceptability curves [53]. Sensitivity analyses to explore uncertainty surrounding ICERs will be also conducted.

It is important to note that we originally planned to have two co-primary economic outcomes (cost-utility analysis (CUA) and cost-effectiveness analysis (CEA)); however, after initiating the trial, following consultation with expert colleagues, we decided that it would be better to have a single primary economic analysis, i.e. the CUA, and consider both the two CEAs as secondary. This is not only because the outcome of the CUA is what NICE prefers, but also to avoid not being able to come to a meaningful conclusion should the CUA and the CEA show contrasting results. This change was approved by the study ethical approval body on 20/9/2022.

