### Interventions

#### Explanation for the choice of comparators {6b}

The comparator is COVID-19 treatment as usual, i.e. whatever treatment the participating services are delivering to treat child anxiety problems in the COVID-19 context.

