#### Intervention description {11a}

The study intervention is OSI (Online Support and Intervention for child anxiety) with therapist support. OSI is an online adaptation of an evidence-based brief parent-guided CBT programme for the treatment of anxiety problems in preadolescent children. OSI comprises a parent website, an accompanying therapist case management system, and an accompanying child game app (see https://osiresearch.org.uk/osi/). The 7 modules are supported by weekly* 20-min telephone/video call sessions between the parent and a therapist and a review session 4 weeks after the final treatment session (*although this may be adjusted by parents/clinicians if required).

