### Participant timeline {13}

Where parents and their children provide online consent or assent, respectively, they will be asked to complete online baseline assessments (all questionnaires), prior to randomisation. After randomisation, parents will be asked to complete a further short questionnaire about treatment expectations and acceptability. Treatment in both arms will be organised by the clinical teams who will be requested to start as soon as possible and at most within 12 weeks of randomisation. Families allocated to the intervention arm will access OSI and a member of the clinical team will provide support as they work through each OSI module. Participating parents and children in both arms (OSI+therapist support and C-TAU) will be sent a link to complete post-treatment and follow-up assessments (questionnaires) online 14 and 26 weeks after randomisation.

Therapists will provide information on COVID-19 treatment as usual for each participant at the start of their treatment within the therapist treatment logs in order for us to be able to describe what services are delivered in the COVID-19 context, specifically the treatment approach being followed, who they are having contact with (e.g. child, parent, both), and for how long.

Therapists will provide brief demographic information at the study outset, will record information on activity with each participating family, and will complete a brief questionnaire about their experience of the treatment after completing treatment with each participating family.

We will also conduct qualitative interviews with a subgroup of parents and therapists/supervisors (*n*= 25–40), between 14 and 26 weeks after randomisation, purposively sampled on the basis of demographics, and we will continue to sample to ensure variability in treatment outcomes across both arms, if possible, to explore and to understand therapist and parents’ experiences of treating child anxiety in this context.

SPIRIT schedule of enrolment, interventions, and assessments

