Therapist Economic Logs (Supervision Logs and Treatment Logs): We will collect economic logs from therapists during the treatment phase (up to 26 weeks if applicable; in the C-TAU arm where there is no set end point to the treatment). Therapists in both trial arms will be asked to complete an economic log throughout treatment, to record all staff-time spent on treatment-related activities (e.g. training and supervision, preparation of sessions, administration, phone contact with parent, video-contact with child whenever applicable).

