### Methods in analysis to handle protocol non-adherence and any statistical methods to handle missing data {20c}

#### Analysis populations

The primary analysis population is defined as all participants for whom data are available analysed according to the groups they were randomly allocated to, regardless of treatment compliance. They must have completed their assessment within 4 weeks of the 14-week and 26-week time points.

A per-protocol analysis will also be carried out excluding those who have deviated from the protocol. Compliance with protocol to be included in the per-protocol analysis will be defined as completing a minimum of the first 5 treatment sessions for participants in either arm (for OSI this is sessions 0, 1, 2, 3, and 4). Other analysis populations will be prespecified in the SAP.

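### Missing therapist contacts are treated as highly deterministic and filled by a conditional mean in both arms, but C-TAU contacts are open-ended by the protocol's own account, so the uncertainty of that cost component would be understated

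*Protocol article*

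**What the plan says.** The Health economics analysis section uses two methods for missing data. On the first it states: "Missing data will be imputed by use of conditional mean imputation for missing values deemed highly deterministic (e.g. online/ face-to-face therapist contacts". The second is "multiple imputation for other variables (e.g. GP consultations) under the assumption of missing at random". Therapist contacts are the named example for the first method, and the sentence does not separate the arms. The section defers detail to a health economics analysis plan (HEAP), to be finalised before any analysis.

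Other sections describe how therapist contact arises:

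- Explanation for the choice of comparators {6b}: C-TAU is "whatever treatment the participating services are delivering to treat child anxiety problems in the COVID-19 context".
- Participant timeline {13}: for C-TAU, therapists log "specifically the treatment approach being followed, who they are having contact with (e.g. child, parent, both), and for how long".
- Health economic measures, on the therapist logs: logs run up to 26 weeks if applicable, "in the C-TAU arm where there is no set end point to the treatment".
- Background and Intervention description {11a}: OSI has 7 calls of 20 minutes plus a review session. Of the weekly timing, the protocol says "although this may be adjusted by parents/clinicians if required".
- Analysis populations: per-protocol status means "completing a minimum of the first 5 treatment sessions for participants in either arm".

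**The concern.** Conditional mean imputation is harmless when the missing value follows almost exactly from other recorded data. The protocol asserts this for therapist contacts, but its description of C-TAU points the other way: the approach, the people seen and the duration differ between services and families, and treatment stops at no fixed point.

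If the value is not nearly determined, a conditional mean gives every family with missing data its predicted value with no scatter, and the analysis then treats that prediction as observed. Given a sound prediction model and data missing at random, the estimated mean need not be biased. What suffers is the standard error.

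Therapist time enters total cost per patient, which enters the cost-utility analysis, the primary economic analysis. The Background section also gives reduced therapist contact time as the reason for delivering the treatment online. The reported precision of incremental cost and the sharpness of the acceptability curve could therefore look better than the data justify.

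**Working it through.** The plan gives no figure on this point to reproduce. The check has two parts.

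**1. Does the premise hold in each arm?**

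- *C-TAU.* Content is whatever the service provides, contact is logged per family so that the trial can describe it, and there is no set end point. Nothing recorded elsewhere fixes the number or length of contacts. The premise fails.
- *OSI.* The design gives 7 × 20 = 140 minutes of calls plus a review of unstated length. The permitted adjustment concerns the weekly pace, which by itself changes neither number nor length. The threshold of five sessions does imply that sessions completed vary. The premise is arguable, but not exact where sessions completed are unknown.
- *Can the sentence be confined to OSI?* It names no arm. Its example includes face-to-face contact, whereas OSI support is by telephone or video call, so the example fits C-TAU at least as well.

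**2. How large is the loss of variance?**

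Let m be the share of families with contacts missing and R² the share of contact variance that the imputation model explains. Take missingness as completely at random, for simplicity. In units of σ²/n for one arm:

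- variance reported after single mean imputation ≈ (1 − m) + m·R²
- actual variance of the estimated mean ≈ (1 − R²)/(1 − m) + R²
- SE ratio = √(reported / actual)
- coverage of a nominal 95% interval = 2Φ(1.96 × ratio) − 1

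Both m and R² are assumptions. The 30% in Sample size {14} is an attrition allowance for families and says nothing about logs that therapists complete; here 30% serves only as the upper end of an assumed range.

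Worked case, m = 0.3 and R² = 0.3: reported = 0.7 + 0.09 = 0.79; actual = 0.7/0.7 + 0.3 = 1.30; ratio = √(0.79/1.30) = 0.78; coverage 87%.

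| m | R² = 0 | R² = 0.3 | R² = 0.6 | R² = 0.9 |
|---|---|---|---|---|
| 10% | 0.90 (92%) | 0.93 (93%) | 0.96 (94%) | 0.99 (95%) |
| 20% | 0.80 (88%) | 0.86 (91%) | 0.91 (93%) | 0.98 (94%) |
| 30% | 0.70 (83%) | 0.78 (87%) | 0.87 (91%) | 0.96 (94%) |

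Only R² = 1 gives a ratio of 1. A simulation of a two-arm difference (245 per arm, regression imputation by arm, assumed SDs of 2 and 5 contacts) agreed: for m = 30% and R² = 0.3, ratio 0.77 and coverage 86%; for m = 20% and R² = 0.3, ratio 0.86 and coverage 90%.

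**Dilution.** These ratios concern the contact component only. Suppose, for illustration, that contacts supply 25% of the variance of net benefit and that the rest is independent and correctly handled. With m = 20% and R² = 0.3, the component's variance ratio is 0.86/1.175 = 0.73. The overall SE ratio is √(0.75 + 0.25 × 0.73) ≈ 0.97, with coverage of about 94%. With m = 30% and R² = 0, the overall ratio is √(0.75 + 0.25 × 0.49) ≈ 0.93, with coverage of about 93%.

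**The case against.** The strongest reply is that the wording is conditional. Mean imputation is for values judged highly deterministic, contacts are only an example, and the HEAP is to supply the detail. A sensible analyst might use the method only for gaps inside a returned log, such as the length of a session known to have taken place. That use would be sound. But the article names the variable and excludes neither C-TAU nor wholly missing logs, so a HEAP that follows it would inherit the problem. This is a stated choice, not an omitted detail.

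Second, therapists complete the logs during treatment, so few may be missing, and OSI contacts may be well predicted. Both points stand, and they limit the size.

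Third, the article does not say how sampling uncertainty will be computed. Repeating the imputation inside each bootstrap sample would largely recover the variance. This also stands, but no such step is stated.

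Some stronger readings are tempting and are not supported:

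- *That therapist contact is the main cost, or the largest cost difference between arms.* The Background section says only that online delivery should reduce contact time. No cost comparison with C-TAU is given.
- *That the understatement is proportionally larger in C-TAU because contacts vary more there.* The SE ratio depends on m and R², not on the size of the variance. The absolute shortfall would be larger if C-TAU contacts do vary more, but no standard deviations are given.
- *That the adjustable OSI schedule shows OSI contacts to be unpredictable.* That note concerns pace.

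**Conclusion.** The point holds for C-TAU. The protocol assigns conditional mean imputation to therapist contacts on a premise that its own description of usual care contradicts. The direction is clear: where contact number or time is truly unknown, the standard error of the contact-cost component is too small.

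The size is not known. Over the assumed range (10–30% missing, R² of 0 to 0.9) the component's SE ratio runs from about 0.99 to 0.70. A reader might carry the lowest coverage in the table, 83%, over to incremental cost or the acceptability curve. The documents do not support that: the figure needs 30% missing and no predictability, and it applies before dilution by the other costs and by QALYs. The effect on the economic conclusions depends on the component's share of variance and is small if few logs are missing. For OSI the concern is confined to families whose number of completed sessions is unknown. The clinical analysis and the sample size are not affected.

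**What to change.** In the HEAP, place unknown therapist contact number and time in the multiple-imputation model already planned for other resource use. Do this at least for C-TAU, and for OSI where the sessions completed are unknown. Impute by arm, with service type and other observed predictors in the model; predictive mean matching is one suitable method. Keep conditional mean imputation only for values that follow from other recorded data, such as the length of a session logged as delivered.

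The cost is a sentence or two of HEAP wording, a few more variables in the imputation model and slightly wider reported uncertainty. No new data are needed.

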### Interim analyses {21b}

#### Decision points

Due to the rapid nature of the trial, there will be no interim analyses.

#### Stopping rules

Due to the rapid nature of the trial, there is not an internal pilot and there are no formal stopping criteria.

### Methods for additional analyses (e.g. subgroup analyses) {20b}

No further analyses are specified at the moment but full details of all analyses will be provided in the Statistical Analysis Plan.

### Methods in analysis to handle protocol non-adherence and any statistical methods to handle missing data {20c}

#### Analysis populations

The primary analysis population is defined as all participants for whom data are available analysed according to the groups they were randomly allocated to, regardless of treatment compliance. They must have completed their assessment within 4 weeks of the 14-week and 26-week time points.

A per-protocol analysis will also be carried out excluding those who have deviated from the protocol. Compliance with protocol to be included in the per-protocol analysis will be defined as completing a minimum of the first 5 treatment sessions for participants in either arm (for OSI this is sessions 0, 1, 2, 3, and 4). Other analysis populations will be prespecified in the SAP.

#### Procedure for accounting for missing, unused, and spurious data

The availability of the primary outcome data will be summarised by randomised group. The mixed effects model implicitly accounts for data missing at random; however, the data missingness mechanism will be explored. Logistic regression models will explore any association between baseline characteristics and availability of the primary outcome. Missing primary outcome data will be reported overall and by randomised group. Covariates found to be predictive of missingness (*P* < 0.05) will be included in the analysis model in a sensitivity analysis of the primary outcome.

The response rates may differ between the intervention arms of the trial. A sensitivity analysis will be conducted that assumes data are missing not at random (MNAR).

#### Procedures for reporting any deviation(s) from the original statistical plan

Any deviations from the original statistical plan for the primary analysis will be discussed and agreed with the Trial Steering Committee and their agreement will be minuted. Deviations will be explicitly reported in subsequent trial reports.

#### Plans to give access to the full protocol, participant-level data, and statistical code {31c}

Anonymised trial data will be made available for open access on completion of the trial. Qualitative interviews will not be shared in this way due to the difficulties in fully anonymising the data. The Statistical Analysis Plan will be made available as a supplementary document to the main paper. Participant-level data and statistical code will be available upon request.

## Oversight and monitoring

### Composition of the coordinating centre and trial steering committee {5d}

The Trial Steering Committee (TSC) comprises relevant subject and methods experts and Patient and Public Involvement (PPI) representatives. We have agreed on terms of reference for the TSC. The TSC will meet every 4 months throughout the study or as necessary in agreement with TSC.

### Composition of the data monitoring committee, its role, and reporting structure {21a}

Recruitment to the trial will be rapid and no interim analyses are planned so a separate Data Monitoring and Ethics Committee will not be formed; however, we reserve the option to form one if the TSC deem it necessary at any point during the trial.

### Adverse event reporting and harms {22}

#### Definition of serious adverse events

A serious adverse events (SAE) is any untoward medical occurrence that:Results in deathIs life-threateningRequires inpatient hospitalisation or prolongation of existing hospitalisationResults in persistent or significant disability/incapacityConsists of a congenital anomaly or birth defect

Other ‘important medical events’ may also be considered a serious adverse event when, based upon appropriate medical judgement, the event may jeopardise the participant and may require medical or surgical intervention to prevent one of the outcomes listed above.

NOTE: The term ‘life-threatening’ in the definition of ‘serious’ refers to an event in which the participant was at risk of death at the time of the event; it does not refer to an event which hypothetically might have caused death if it were more severe.

There is a very low risk of SAEs in the current trial; however, the following details a non-exhaustive list of potential SAEs and adverse vents (AE):

#### Potential serious adverse events (SAEs) (to parent/child)

Admission to a psychiatric hospital (parent/child).Sectioned under the Mental Health Act.Significant and sustained deterioration of pre-existing mental health condition that requires immediate intervention that cannot be accommodated within the treatment protocol (as determined in clinical supervision).Diagnosis of new mental health condition.Suicidal behaviour.A serious safeguarding issue is revealed.

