#### Criteria for discontinuing or modifying allocated interventions {11b}

During the course of the study, a participant may choose to withdraw early from the study treatment at any time. This may happen for several reasons, including but not limited to:The occurrence of what the participant perceives as an intolerable adverse event (AE)Inability to comply with the study proceduresParticipant decision

In the case of participant withdrawal, we will retain data collected only until that point unless the participant requests otherwise or agrees to take part in further assessments.

It is also possible that the clinical team might withdraw the participant from the research treatment (OSI+therapist support) if allocated. If the therapist delivering treatment feels the child should not continue with OSI+therapist support (e.g. due to serious comorbidities arising that need to be addressed), we will retain the data and continue to invite the participant to take part in further assessments, unless the participant requests otherwise.

The number of withdrawals from treatment and/or follow-up measures will be logged with a summary of their reasons (if offered by the participant).

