#### Strategies to improve adherence to interventions {11c}

Therapists will receive a video-based training programme (45 min) and a treatment manual prior to delivering treatment within the study. All teams will be offered regular question and answer sessions throughout the treatment delivery phase to support set-up and delivery. Clinical supervision will be provided within teams following their usual procedures.

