## Assignment of interventions: blinding

### Who will be blinded {17a}

Due to the nature of the trial, blinding to condition is not possible to the trial participants or research team; however, the statistical analyses will be conducted blind to trial condition.

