#### Adverse events reporting opportunity

Trial therapists will be asked to report any adverse events that they become aware of while working with families in either arm over the whole treatment period. We will also provide parents and children an opportunity to describe any negative impacts of participating in the study after completing the questionnaires at 14 and 26 weeks and, for participating parents, after completing the qualitative interview. So as not to ‘lead’ answers, we will enquire about both the positive and negative consequences of taking part in the treatment. The research team will regularly review responses to identify any responses that indicate the presence of an adverse event.

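### The SAE item for deterioration is tied to a treatment protocol that usual care does not have, so the same event may be classified differently by arm

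*Protocol article*

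**What the plan says.** The Protocol article, under Potential serious adverse events (SAEs) (to parent/child), lists six items. Five carry no condition about treatment: psychiatric admission, sectioning, a new mental health diagnosis, suicidal behaviour and a serious safeguarding issue. The sixth, worsening of an existing mental health condition, applies when the worsening "requires immediate intervention that cannot be accommodated within the treatment protocol (as determined in clinical supervision".

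The two arms are described very differently:

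- **OSI**, under Intervention description {11a}: "The 7 modules are supported by weekly* 20-min telephone/video call sessions between the parent and a therapist and a review session". The section adds that the weekly schedule may be adjusted.
- **C-TAU**, under Explanation for the choice of comparators {6b}: "whatever treatment the participating services are delivering to treat child anxiety problems in the COVID-19 context". The paragraph on therapist economic logs, under Health economic measures, says that logs run up to 26 weeks "in the C-TAU arm where there is no set end point to the treatment".

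On who decides, Strategies to improve adherence to interventions {11c} states: "Clinical supervision will be provided within teams following their usual procedures". Under Implementation {16c}, the allocation is emailed to the clinical team. Under Who will be blinded {17a}, "blinding to condition is not possible to the trial participants or research team".

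**The concern.** An SAE criterion that is to be compared between arms should describe what happened to the participant. This one also asks whether the treatment being given could cope. That question has a reasonably clear meaning in OSI, where the content is set out. It has no stated meaning in C-TAU, where the article describes no treatment protocol and treatment may change as the service sees fit.

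At stake is the comparability of SAE counts. OSI is a remote treatment with little therapist contact, and it is to be judged non-inferior to usual care. Whether more children deteriorate seriously is a natural safety question for such a trial. The article expects very few SAEs, so a handful of events classified by different standards could shape how the two arms look side by side. The SAE label also decides whether an event enters the step at which reporting to the ethics committee is considered.

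**Working it through.** The article states no figure on this point, so the check is a comparison of its sections.

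**Step 1: the same event in each arm.** Take a child whose existing condition worsens markedly and lastingly, who needs prompt intervention, and who is managed in the community without admission, new diagnosis, suicidal behaviour or a safeguarding issue.

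- *In OSI.* The package is modules, short parent sessions and a review. A team could readily conclude that the intervention needed lies outside it. Criteria for discontinuing or modifying allocated interventions {11b} points the same way: it foresees that "the clinical team might withdraw the participant from the research treatment (OSI+therapist support) if allocated", giving newly arising serious comorbidity as an example. The item is then met.
- *In C-TAU, reading A.* The team adds or changes sessions. Since C-TAU is whatever the service delivers, this is still C-TAU. The need has been accommodated and the item is not met.
- *In C-TAU, reading B.* The team reasons that there is no protocol that could accommodate anything. The item is met for every such worsening.
- *In C-TAU, reading C.* The team judges against the approach that its therapist recorded at the start of treatment (Participant timeline {13}). The answer then varies by site and therapist.

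Nothing in the article chooses between A, B and C.

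**Step 2: is there a later step that evens this out?** Under Adverse event reporting and harms {22}, the clinical team and the PI investigate reported events, and the PI and the trial management group log and monitor them. That brings in a central view, but the research team is not blinded and the article gives no rule for applying the clause in C-TAU. No separate data monitoring committee is planned ({21a}).

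**Step 3: can the effect be sized?** Let n be the number per arm, r the true rate of such worsening (taken as equal in both arms), and p(OSI) and p(C-TAU) the shares classed as SAEs under this item. The spurious difference in counts is

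n × r × [p(OSI) − p(C-TAU)].

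Only n is in the article: 209 to 280 per arm. Assuming r between 1% and 5%, with 3% as a middle value:

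- 0.01 × 209 = 2.1 events per arm at the low end
- 0.03 × 209 = 6.3 to 0.03 × 280 = 8.4 in the middle
- 0.05 × 280 = 14 at the high end

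The bracket can lie anywhere from −1 to +1, so under these assumptions the difference can lie anywhere from −14 to +14 events. The documents give neither r nor either share. The formula shows that the size and sign come entirely from what is assumed.

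**The case against.** The strongest reply is that this is one item in a list that the article itself calls non-exhaustive, and that other routes are the same in both arms:

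- The general SAE definition, including important medical events by medical judgement, does not mention allocation.
- The other five listed items carry no such condition.
- Therapists are asked to "report any adverse events that they become aware of while working with families in either arm over the whole treatment period", and parents and children can report at 14 and 26 weeks.
- The AE list includes a sustained increase in detrimental behaviours, and the emergence of new ones.
- All AEs are logged, and an AE reported more than once for a participant, or more than three times in the study, is treated as an SAE.
- CAIS-P, RCADS, SDQ-P and ORS are collected on the same schedule in both arms, so average worsening is measured whatever the SAE label.

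All of this stands, and it rules out three stronger readings that a reader might infer. The first is that deterioration can be an SAE only through this clause; the general definition and the other items say otherwise. The second is that deterioration under usual care goes uncounted; it can be logged as an AE and upgraded. The third is that the trial will show a false safety disadvantage for OSI of some stated size. Reading B shows that the direction is not fixed, OSI is not shown to absorb nothing (session timing is adjustable and concomitant care is unrestricted), and the article describes no formal between-arm SAE analysis.

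The reply does not remove the arm-dependence. Community-managed worsening need not meet the general definition. The important-medical-event route is discretionary. The other five items are different events. The repeat rule helps only if a team that has absorbed the event logs it as an AE first.

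**Conclusion.** The point holds in a limited form. As written, the item's threshold refers to a treatment protocol that is described for OSI and not for C-TAU, and it is applied by teams who know the allocation. The same deterioration may be classed as an SAE under this item in one arm and not in the other. More SAEs in OSI is the likelier direction, because a fixed package is easier to exceed than open-ended care, but that is an inference about how teams will read the clause. No magnitude follows from the documents.

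The conclusion assumes that no form guidance or other trial document, not shown here, already tells C-TAU teams how to apply the clause. It concerns event classification and leaves the primary outcome analysis untouched. It is worth correcting before SAEs are tabulated by arm, because the remedy is cheap and the expected number of events is small.

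**What to change.** Reconcile the deterioration item with {6b}, {11a} and the statement that C-TAU has no set end point, so that the recording criterion describes the severity of the event without reference to the allocated treatment and is applied identically in both arms. Where it is useful to know that the allocated treatment could not accommodate the event, record that as a separate field on the AE/SAE form.

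Apply the same wording to events already logged in both arms. The 100% verification of AE/SAE entries planned for the end of the trial (Dataset reviews) is a convenient point. Because recruitment closed on 03/08/2022 and the research team is unblinded, reclassification carries its own risk of bias. It should preferably be done without sight of allocation, with treatment details that reveal the arm masked where possible.

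The cost is a change to the SAE list and form guidance, a re-read of logged events, and possibly higher SAE counts. No new visits or measures are needed. The change affects classification for reporting only and alters nothing in how any child is managed.
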